### CMAM counseling

Standard CMAM counseling will be provided to caregivers about the proper consumption of their nutritional supplementation, including the need to consume the daily allotment at multiple small feedings through the course of the day prior to feeding home foods, the need to continue breastfeeding (if still breastfeeding), the need for availability of clean water while feeding, sanitation and hygiene reminders, the importance of not sharing the supplements with siblings or others, and signs of clinical worsening that would warrant an urgent return to the health post or health center.

To improve adherence to the assigned intervention group and decrease the risk of crossover, additional counseling will be provided to caregivers regarding the importance of respecting the randomization process and the feasible safety of all intervention groups. Scripting in the field will emphasize the nature of the interventions as *medicine* (rather than food) customized for each individual child’s specific illness, based on their severity of acute malnutrition and randomization group. At each follow-up visit, the total number of sachets consumed will be asked of the caregivers and empty sachets will be collected from the caregiver. Informal discussions with local village health care workers, community leaders, and individual caregivers have all suggested that the caregivers in the study areas will understand, and be accepting of, randomization that may lead to varying amounts of intervention foods to each child.

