### Intervention trials 1 and 2 sample size

The powered objective for the AM intervention trials will be the rates of anthropometric recovery by 16 weeks (Table 2), comparing each intervention group individually against the standard of care (control) group, based on the hypothesis that the novel interventions are non-inferior.

A 2020 systematic review of treatment outcomes among children treated for SAM as outpatients with the standard dosing of RUTF showed an average recovery rate of 70% [24]. In Ethiopia specifically, a recent study in Gondar found approximately 75% of children with SAM treated as outpatients recovered [25]. Another recent study in Oromia found that children enrolled by MUAC alone had a recovery rate of approximately 85% [26]. Less complete outcome data exists for children with MAM, but an operational study from southern Ethiopia demonstrated a 73% recovery rate for children with MAM treated with RUSF [27]. Based on these accumulated data, we have powered the study based on an anticipated recovery rate of 75% for both the SAM and MAM studies.

The non-inferiority margin that is considered clinically acceptable is a relatively subjective judgment that needs to incorporate local sociocultural preferences and economic considerations. Trial cost and duration limitations must also be considered. To help inform this decision, we conducted interviews with health care workers and community leaders within Ethiopia, as well as discussions with our technical advisory groups. There was consensus that a non-inferiority margin of 5–10% would be considered clinically useful, although there was a notable preference for as small of a margin as would be feasible to provide the most robust data, especially compared to prior trials of modified dosing regimens which have used comparatively larger non-inferiority margins. Given resource constraints, we will thus aim for a non-inferiority margin of 6% for each trial, but may have to compromise to up to 10% if enrollment challenges arise.

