The α parameter (Type I error) will be set at 0.05, indicating a 5% risk of identifying a difference between an experimental group and the control group where none really exists. The β value (Type II error) will be set at 0.20, thereby giving a power of 80% to identify a difference between an experimental group and the control arm. Due to possible incorrect enrollments, incomplete or inaccurate data collection, and/or drop-outs, we will aim to enroll an additional 10% in each study arm beyond the sample size target calculation.

Based on these parameters, we determined that the minimum sample size needed for a non-inferiority margin of 6% is 798 children per study arm; the minimum needed for a non-inferiority margin of 8% is 462 children per study arm; for 10%, the minimum needed for 10% would be 305 [28]. Multiplying the largest of these by three study arms per trial gives a targeted sample size for enrollment of 2400 children in each trial. This warrants an enrollment of an average of 140 children per month in each trial. If enrollment is slower than anticipated, requiring an adaptation to the enrollment goal, then 1400 children in each trial will be sought to achieve a non-inferiority margin of 8% in a three-armed trial, or 915 for a 10% non-inferiority margin.

### Post-recovery– trial 3

Children from all 3 arms in each of the 2 AM intervention trials who achieve anthropometric recovery within 16 weeks of enrollment will then be offered enrollment into the third of the three integrated trials encompassed by the MODAM study (Fig. 1). This post-recovery trial aims to offer insights into numerous outstanding questions in the AM field, given that high rates of post-recovery relapse and mortality place heavy burdens on operational SAM and MAM treatment programs [16, 29]. High post-SAM relapse is a notable problem in Ethiopia, where such cases make up a high proportion of CMAM enrollments [30–32].

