### Statistical analyses

Standard statistical approaches will be used in each of the three trials to analyze each intervention arm independently in comparison to the control arm. Dichotomous variables will be compared using Chi-square testing. Continuous variables will be analyzed using the Student t-test. Rates of recovery and relapse will be evaluated using Kaplan-Meier survival analyses. Regression analyses will be used as appropriate to control for confounding variables. In general, P values less than 0.05 will be considered statistically significant, although this will be reduced in the case of multiple comparisons. 95% confidence intervals will be calculated in addition to P values in order to provide additional detail about error margins in the various calculations. Intention-to-treat analyses will be used throughout, as this will provide the most pragmatic and applicable evidence to inform the real-world scale-up of these interventions.

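### Trials 1 and 2 are powered for non-inferiority, but the stated error rates and the chi-square test at P<0.05 are those of a test for a difference, and no stated rule uses the margin

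*Protocol article*

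**What the plan says.** **Hypothesis.** In the protocol article, the section Intervention trials 1 and 2 sample size makes recovery by 16 weeks the powered objective. Each experimental arm is compared with control, "based on the hypothesis that the novel interventions are non-inferior". On the margin it says "we will thus aim for a non-inferiority margin of 6% for each trial", adding that the team "may have to compromise to up to 10% if enrollment challenges arise". The planning rate is 75% recovery in both trials.

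**Error rates.** The same section sets alpha at 0.05, "indicating a 5% risk of identifying a difference between an experimental group and the control group where none really exists", and describes the 80% power as power to identify a difference. It does not say whether alpha is one- or two-sided. It gives 798, 462 and 305 children per arm for margins of 6%, 8% and 10%.

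**Analysis.** The section Statistical analyses states: "Dichotomous variables will be compared using Chi-square testing". It assigns Kaplan-Meier methods to rates of recovery and takes P<0.05 as significant, to be lowered for multiple comparisons. It adds 95% confidence intervals as extra detail beside the P values. On the analysis set it says "Intention-to-treat analyses will be used throughout", giving as its reason that this is the most pragmatic evidence for scale-up.

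**The concern.** Recovered versus not recovered is dichotomous, so the test named for it is chi-square, whose null hypothesis is equal recovery. Non-inferiority needs the opposite null: that the experimental arm is worse by at least the margin. A non-significant chi-square does not reject that null, and a significant one does not show that the loss exceeds the margin.

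The error definitions have the same fault. In a non-inferiority comparison, alpha is the risk of accepting an arm that is worse by the margin, and power is the chance of accepting an arm that is truly equal. The article defines both for finding a difference. That is a misstatement on the page, and a separate analysis plan could correct it only by contradicting the article.

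The results are meant to inform national protocols and WHO guidance. If 'no significant difference' came to stand for 'non-inferior', a regimen with materially lower recovery could be endorsed.

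**Working it through.** **Inputs from the article.** Control recovery 75%; margins m of 6, 8 and 10 points; n = 798, 462 and 305 per arm; 80% power; alpha 0.05 with sidedness unstated; 10% inflation; equal allocation.

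**1. The plan's own sample sizes.** The formula for detecting a difference (75% vs 75% minus m), one-sided 0.05, 80% power, continuity-corrected and multiplied by 1.10, gives:
- 6%: 725 × 1.10 = 798 (stated 798)
- 8%: 422 × 1.10 = 465 (stated 462)
- 10%: 279 × 1.10 = 307 (stated 305)

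The usual non-inferiority formula, n = 2 × 0.75 × 0.25 × (z_alpha + 0.842)² / m², gives without inflation:
- one-sided 0.025: 818, 460 and 295
- one-sided 0.05: 645, 363 and 232

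The difference formula fits all three stated figures best. This is inference about how the numbers were obtained, but it agrees with the way the article words alpha and power.

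**2. How often chi-square misses a deficit equal to the margin.** With p1 = 0.75, p2 = 0.75 − m and p̄ their mean:

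SE0 = √[2p̄(1−p̄)/n], SE1 = √[(p1(1−p1) + p2(1−p2))/n]

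P(non-significant) = 1 − Φ[(m − 1.96·SE0)/SE1]

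| Margin | n per arm | SE0 | SE1 | Φ argument | Non-significant |
|---|---|---|---|---|---|
| 6% | 798 | 0.02248 | 0.02243 | 0.711 | 24% |
| 8% | 462 | 0.02986 | 0.02974 | 0.722 | 24% |
| 10% | 305 | 0.03711 | 0.03689 | 0.739 | 23% |

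A rule built on the margin would pass such an arm in 2.5% of trials (two-sided 95% interval) or 5% (90% interval). If the 10% inflation is lost (798/1.10 ≈ 725), the first figure becomes 28%. Lowering the P threshold for multiple comparisons would raise all of them.

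**3. Two possible results at 798 per arm.**
- Observed 75% vs 71%: SE0 = 0.02223, z = −0.04/0.02223 = −1.80, P = 0.07. The 95% interval is −0.04 ± 1.96 × 0.02220, or −8.4 to +0.4 points.
- Observed 75% vs 72%: z = −0.03/0.02209 = −1.36, P = 0.17. The 95% lower limit is −0.03 − 1.96 × 0.02208 = −7.3 points; the 90% lower limit is −6.6.

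Neither differs significantly from control, and neither shows non-inferiority at 6 points.

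**4. Power for the stated hypothesis.** With a true difference of zero at 75% recovery, power = Φ(m/SE − z_alpha), where SE = √(2 × 0.75 × 0.25/n).
- 798 analysed: SE = 0.02168 and m/SE = 2.768. Power is Φ(0.808) = 79% at one-sided 0.025, or 87% at one-sided 0.05.
- 718 analysed (798 × 0.90): SE = 0.02285 and m/SE = 2.625. Power is Φ(0.665) = 75%, or 84%.

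**The case against.** The strongest reply is that Statistical analyses is one short, general paragraph covering three trials and many outcomes, including a post-recovery trial with no stated non-inferiority hypothesis. Its chi-square sentence does not name the primary analysis. It plans 95% confidence intervals, which are what a non-inferiority conclusion needs, and a condensed article may leave the decision rule to an analysis plan. Most of this stands. A reader might infer that the trials cannot test their hypothesis, or that the team will read a non-significant P as non-inferior. The article supports neither: the intervals could carry the test, and no such reading of P is stated. The reply does not rescue the alpha and power definitions, which are wrong for the stated hypothesis, nor the absence of any link between the intervals and the margin.

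A reader might also infer that the error grows sharply as enrolment falls. A 6-point deficit at about 420 or 277 per arm (462 and 305 without the 10% inflation) is missed by chi-square in 51% and 65% of trials. But the article ties those sizes to margins of 8 and 10 points. At the matching margin the rate stays at 23–24% at the stated sizes, or 27–28% without the inflation.

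Finally, it is tempting to say that intention-to-treat alone invalidates the comparison because the plan expects sharing and crossover. The CMAM counseling section describes counselling "To improve adherence to the assigned intervention group and decrease the risk of crossover" and advice against sharing. It gives no expected rate, so no size of dilution can be derived. Intention-to-treat does not prevent a non-inferiority test, and the article gives its reason for choosing it. A per-protocol set depends on behaviour after randomization that may differ by dose, so it suits a supportive analysis better than a second condition for success.

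**Conclusion.** The point holds as a mismatch on the page: a non-inferiority hypothesis, error rates defined for a difference, and a test and intervals that do not use the margin. Its size depends on use. Only if non-significance were taken as non-inferiority would an arm worse by the full margin pass in about 24% of trials, against 2.5% (or 5%) under a correct rule. Restated for non-inferiority at one-sided 0.025, power at the 6-point margin is about 79% with 798 per arm analysed and about 75% after 10% loss, a little short of the stated 80%.

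These figures assume 75% control recovery, a normal approximation and a single two-arm comparison without multiplicity adjustment. The power figures also assume truly equal arms. The 10% loss is the article's own inflation allowance; children lost to follow-up count as not recovered, so the number analysed may fall by less.

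**What to change.** - **Statistical analyses:** for each experimental arm in trials 1 and 2, name the primary analysis as the risk difference (experimental minus control) in 16-week recovery. Conclude non-inferiority only if the lower limit of the two-sided 95% interval (one-sided alpha 0.025) lies above minus the adopted margin. That margin is 6 points, or the 8 or 10 points formally adopted under the enrolment fallback before unmasking. Keep chi-square for superiority and secondary outcomes.
- **Sample size section:** define alpha as the risk of accepting an arm that is worse by the margin, and power as the chance of accepting an arm that is truly equal. State the sidedness and give the power on that basis.
- **Analysis sets:** keep intention-to-treat as primary. Add a supportive per-protocol sensitivity analysis, defined before unmasking from the sachet counts and returned empty sachets already collected, and do not make it a co-requirement.

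The cost is revised wording and one extra analysis of data already collected. The intervals are already planned. The restated power at 6 points is slightly below 80%, which the team would have to accept openly or offset with more children.

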### Anthropometry

Study subjects will be evaluated and enrolled through a series of steps outlined below to ensure consistency and equity for all children encountered. Children’s AM status will be assessed using standard field anthropometric techniques [18]. At screening, enrollment, each treatment follow-up visit, and each post-recovery follow-up visit, all of the following will be evaluated:

• recumbent length using a rigid board, to the nearest 1 mm;

• weight using a digital scale, to the nearest 100 g;

• MUAC using a flexible tape, to the nearest 1 mm; and.

• bilateral pitting edema.

Length and weight will then be evaluated using gender-specific look-up tables to determine their WLZ based on WHO Growth Standards [3]. Children will be classified as having SAM if their WLZ is more than 3 standard deviations below the median, if their MUAC is less than 115 mm, or if they demonstrate bilateral pitting edema. Children will be classified as having MAM if their WLZ is between 3 and 2 standard deviations below the median or if their MUAC is ≥ 115 and < 125 mm, without meeting other criteria for SAM.

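### The methods named for the powered recovery endpoint leave enrollment WLZ, MUAC and edema unused, which costs some precision against the non-inferiority margin but does not bias the comparison

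*Protocol article*

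**What the plan says.** The section on sample size for trials 1 and 2 states: "The powered objective for the AM intervention trials will be the rates of anthropometric recovery by 16 weeks". Each experimental arm is set against control, "based on the hypothesis that the novel interventions are non-inferior". The planning values are a 75% recovery rate ("we have powered the study based on an anticipated recovery rate of 75% for both the SAM and MAM studies") and a 6-point margin ("we will thus aim for a non-inferiority margin of 6% for each trial"), with 8 or 10 points as fallbacks.

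The treatment outcomes section and Table 2 make the endpoint binary. A child has recovered if WLZ is at -2 or better, MUAC is at 125 mm or better and there is no edema, at two consecutive visits within 16 weeks. Every other final outcome counts as not recovered.

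The Anthropometry section has weight, length, MUAC and edema taken on every child: "At screening, enrollment, each treatment follow-up visit, and each post-recovery follow-up visit, all of the following will be evaluated".

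The Statistical analyses section covers all three trials in one general paragraph. Three of its statements bear on recovery:
- "Dichotomous variables will be compared using Chi-square testing".
- Recovery and relapse rates are to be examined by Kaplan-Meier methods.
- "Regression analyses will be used as appropriate to control for confounding variables".

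The same paragraph promises 95% confidence intervals alongside P values. It does not name a covariate, an endpoint for the regression or an effect scale.

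**The concern.** Recovery means crossing fixed thresholds within a fixed time. How far a child starts below those thresholds is a natural predictor of crossing them, and it is known for every child before randomization. The article describes allocation in blocks of 18 within each trial and mentions no stratification by baseline severity, so the design as described does not remove this variation either.

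Both methods named for recovery, chi-square and Kaplan-Meier, ignore it. The regression sentence is aimed at confounding, which randomization already deals with in expectation. The benefit available here is a narrower interval, and that needs a model fixed in advance on the scale of the margin.

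A non-inferiority conclusion turns on the width of the interval for the risk difference. The article calls its enrollment target ambitious, foresees a smaller sample, the loss of an arm or a wider margin, and reports that stakeholders wanted the smallest feasible margin. Precision that needs no extra children has practical value in that setting.

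**Working it through.** **Inputs from the article.** Recovery 75%; margins of 6, 8 and 10 points; stated minimum per arm 798, 462 and 305; power 80%; 10% added enrollment; "The α parameter (Type I error) will be set at 0.05", with sidedness not given.

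**Assumed.** R², the share of variance in recovery explained by the enrollment measures. The article gives no value, so 2% to 20% is used.

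**Step 1: reproduce the stated size.** Compare 75% with 69% by a one-sided 5% test at 80% power. With pooled p = 0.72:

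n = [1.645·√(2·0.72·0.28) + 0.842·√(0.75·0.25 + 0.69·0.31)]² / 0.06² ≈ 692

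The continuity correction, (n/4)·[1 + √(1 + 4/(n·0.06))]², gives 725, and 725 × 1.1 = 797.5, which rounds up to 798. This matches exactly. The same route gives 422 × 1.1 ≈ 465 for 8 points (stated 462) and 279 × 1.1 ≈ 307 for 10 points (stated 305), both close.

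The usual non-inferiority formula, 2·0.75·0.25·(z₁₋α + 0.842)²/margin², gives 818, 460 and 295 at one-sided 2.5% with no dropout allowance, and 645 for 6 points at one-sided 5%. None of these calculations includes a gain from covariates.

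Two things follow. The alpha convention is uncertain, so both are shown below. Also, 798 probably includes the 10% allowance, so the number analysed may be nearer 725.

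**Step 2: unadjusted precision at 798 analysed per arm.**

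SE = √(2·0.75·0.25/798) = 0.02168, so the 95% half-width is 1.96 × 0.02168 = 4.25 points.

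Power = Φ(0.06/0.02168 − z) = Φ(2.768 − z). This is 79.0% with z = 1.960 and 86.9% with z = 1.645.

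**Step 3: adjusted precision.** Take the variance of the standardised risk difference as (1 − R²) times the unadjusted variance, so SE becomes 0.02168·√(1 − R²). The unadjusted size is equivalent to 798·(1 − R²) children per arm with adjustment.

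| Assumed R² | 95% half-width (points) | Power, one-sided 2.5% | Power, one-sided 5% | Adjusted n matching 798 unadjusted |
|---|---|---|---|---|
| 0 | 4.25 | 79.0% | 86.9% | 798 |
| 2% | 4.21 | 79.8% | 87.5% | 782 |
| 5% | 4.14 | 81.1% | 88.4% | 758 |
| 10% | 4.03 | 83.1% | 89.8% | 718 |
| 20% | 3.80 | 87.2% | 92.6% | 638 |

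**Step 4: if only 725 per arm are analysed.** SE = √(0.375/725) = 0.02274, and power at one-sided 2.5% is Φ(0.06/0.02274 − 1.960) = 75.1%. With R² = 10% the SE is 0.02158 and power is Φ(2.781 − 1.960) = 79.4%.

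**Step 5: what these R² values mean.** With one normally distributed baseline predictor in a logistic model and 75% recovery overall, an odds ratio per standard deviation of 1.5, 2 or 3 corresponds to R² of about 3%, 8% or 17%. A gain of 5 power points at one-sided 2.5% needs R² of about 13% (a correlation of about 0.36). That corresponds to roughly 53% recovery in the worst baseline quartile and just over 90% in the best.

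**The case against.** The strongest objection is that this belongs in the SAP. Covariate lists, standardisation and standard-error methods usually sit there, and a journal article condenses. That holds for the details of the model. It does not dispose of the point, because the article states which methods will be used, and those it ties to recovery are unadjusted.

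A second objection is that the regression sentence leaves adjustment open. It does, and a reader might wrongly infer that the plan rules adjustment out or makes chi-square the sole primary analysis. The paragraph is generic, also names Kaplan-Meier for recovery, and excludes no covariate. What remains is that regression is offered for a different purpose, at discretion, without being tied to the powered endpoint or the risk-difference scale.

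A third objection is that nothing here is invalid. This stands in full. A reader might infer a biased comparison or a sample size that fails for want of adjustment. The documents support neither: allocation is individually randomized, and the stated size does not rely on covariates.

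A fourth is that a large gain cannot be taken for granted. This also stands. Death, hospitalization and loss to follow-up count as non-recovery, and distance from the thresholds may predict them poorly. In the MAM trial the entry ranges for WLZ and MUAC are narrow and edema is absent by definition.

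**Conclusion.** The point holds as a matter of efficiency. The methods named for recovery do not use the enrollment values of the measures that define it, and the regression sentence does not fill the gap. The unadjusted analysis remains valid and unbiased.

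At 798 analysed per arm and a 6-point margin, the forgone power is about 1 to 8 percentage points at one-sided 2.5% (79.0% against 79.8% to 87.2%), or about 0.6 to 5.7 points at one-sided 5% (86.9% against 87.5% to 92.6%). Equivalently, it is worth about 16 to 160 children per arm (2% to 20% of 798).

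These figures rest on the assumed R² of 2% to 20%, on 75% true recovery in both arms, on the approximation that variance falls by the factor 1 − R², and on all 798 children being analysed. The MAM trial is likely to sit towards the lower end.

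**What to change.** For recovery by 16 weeks in trials 1 and 2, name one primary analysis: fit a logistic model with arm, enrollment WLZ, MUAC and age, adding enrollment edema in the SAM trial only. Standardise its predictions over the enrolled children to obtain a risk difference for each experimental arm against control, with a robust or bootstrap standard error. Compare the confidence interval with the non-inferiority margin, and state the confidence level so that the alpha convention is clear. This also puts the decision on the margin itself, whereas an ordinary chi-square tests for zero difference. Keep the unadjusted risk difference as a sensitivity analysis, and Kaplan-Meier as a description of time to recovery.

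The cost is a few sentences of analysis text and a few lines of code. No new data are needed, and the sample size can stay as it is. The downside is that covariates and their functional form must be fixed before outcomes are seen by arm, and the return is small if baseline anthropometry predicts recovery weakly.

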### Intervention trials 1 and 2 follow-up visits during treatment

Children will be reassessed at health posts and health centers during follow-up visits every 7 days (SAM trial) or every 14 days (MAM trial) for up to 16 weeks after the time of enrollment, the maximum length of stay prescribed in the Ethiopian national guidelines. At each follow-up visit, a full set of anthropometric measurements will be reassessed, recent infectious symptoms (vomiting, diarrhea, fever, cough) will be queried of the caregiver, and appropriate appetite verified.

Children who appear to be progressing towards recovery will receive additional allotments of their assigned intervention. Children who are not progressing well (e.g., poor weight gain, feeding or health concerns expressed by their caregivers, poor clinical appearance including medical complications, etc.) will be either re-engaged in nutritional and health counseling, including the importance of full adherence to the allocated intervention, or referred to a higher level of care. Clinical assessments for complications will be completed similar to enrollment.

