### Intervention trials 1 and 2 treatment outcomes

At each follow-up visit, children in the AM trials will receive one of the classifications listed in Table 2. Children will be assigned a final discharge outcome of recovery, defined as having a WLZ at two standard deviations below the median or better *and* MUAC at 125 mm or better *and* no edema, all for two consecutive visits. Children will be considered to have not recovered with any of the following discharge outcomes: deterioration to SAM (for children in the MAM trial), death, hospitalization, lost to follow-up, and remaining with AM after 16 weeks of treatment.

**Table 2 Tab2:** Follow-up visit outcomes for AM intervention trials

	SAM Trial	MAM Trial	Definition

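### Kaplan-Meier is named for recovery rates, but the powered endpoint counts early exits as not recovered; under ordinary censoring recovery is overstated and the arm difference is distorted in either direction

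*Protocol article*

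**What the plan says.** All references are to the protocol article.

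- **Objective** (Intervention trials 1 and 2 sample size): "The powered objective for the AM intervention trials will be the rates of anthropometric recovery by 16 weeks". Each experimental arm is compared with control, "based on the hypothesis that the novel interventions are non-inferior". The planning recovery rate is 75%, and the target margin is 6%, with 8% or 10% as fallbacks.
- **Endpoint** (Intervention trials 1 and 2 treatment outcomes, with Table 2): "Children will be considered to have not recovered with any of the following discharge outcomes". The list is deterioration to SAM (MAM trial only) and then "death, hospitalization, lost to follow-up, and remaining with AM after 16 weeks of treatment". The endpoint is thus a yes/no classification of every enrolled child.
- **Follow-up** (Intervention trials 1 and 2 follow-up visits during treatment): visits take place "every 7 days (SAM trial) or every 14 days (MAM trial) for up to 16 weeks after the time of enrollment".
- **Analysis** (Statistical analyses): "Rates of recovery and relapse will be evaluated using Kaplan-Meier survival analyses". The same paragraph says "Dichotomous variables will be compared using Chi-square testing" and "Intention-to-treat analyses will be used throughout".

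The paragraph does not say which method carries the non-inferiority comparison. It states no censoring rule for children who die, are hospitalized, deteriorate or are lost, and it names no competing-risk method. The only censoring that the article mentions is in Data and safety monitoring, for children in an arm closed on the board's advice.

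**The concern.** The method sentence uses the same term, rates of recovery, as the powered objective. A reader would reasonably take Kaplan-Meier to be the method for that objective.

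The method and the endpoint then treat the same children differently. Under Table 2, a child who dies or is hospitalized in week 5 is a failure and stays in the denominator. In a standard Kaplan-Meier analysis of time to recovery, that child is censored in week 5 and is implicitly assumed to recover later at the rate of the children still in treatment. For a child who has died this cannot be true. For the other exits it contradicts the classification in Table 2.

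Two things are at stake. The level of recovery would be overstated in every arm that has exits. The difference between arms, on which the 6% margin is judged, would depend on why an arm fails as well as on how often.

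**Working it through.** **1. The plan's own figure.** Take 75% against 75% minus the margin, one-sided alpha 0.05, power 80%, the two-proportion formula with continuity correction, then add 10%:

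| Margin | n before inflation | n × 1.10 | Stated |
|---|---|---|---|
| 6% | 725 | 798 | 798 |
| 8% | 422 | 465 | 462 |
| 10% | 279 | 307 | 305 |

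The first is exact and the others are within 1%. The sample size therefore rests on a comparison of proportions, not on survival methods.

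**2. One minus Kaplan-Meier with exits censored.** Let R be the proportion who recover by week 16 and E the proportion who exit early. The rest remain with AM at week 16. R = 75% for control is the plan's figure. R = 69% for the experimental arm is a true deficit equal to the margin. All values of E are assumptions.

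Spread recoveries and exits evenly over weeks 2 to 16 (15 weeks), with recoveries counted before exits within a week. Then r = R/15, e = E/15, and the proportion at risk at step j is N(j) = 1 − (j − 1)(r + e). The estimate is 1 − product over j = 1 to 15 of [1 − r/N(j)].

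| Arm | R / E / remaining (%) | r | e | N(15) | 1 − KM | KM deficit |
|---|---|---|---|---|---|---|
| Control | 75 / 15 / 10 | 0.050 | 0.010 | 0.160 | 84.7% | – |
| Deficit all through exits | 69 / 21 / 10 | 0.046 | 0.014 | 0.160 | 82.0% | 2.7 points |
| Half through exits | 69 / 18 / 13 | 0.046 | 0.012 | 0.188 | 79.5% | 5.2 points |
| Slower recovery, equal exits | 69 / 15 / 16 | 0.046 | 0.010 | 0.216 | 77.3% | 7.4 points |

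The true deficit is 6.0 points in every row. For the all-exits row, other exit timings gave apparent deficits from 1.1 points (early exits) to 5.8 points (late exits).

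**3. The same estimator with exits kept in the risk set as never recovered.** Now N(j) = 1 − (j − 1)r, each factor is N(j + 1)/N(j), and the product telescopes to 1 − R. The estimates are 75% and 69%, exactly the Table 2 proportions. The distortion comes from the censoring, not from Kaplan-Meier as such.

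**4. A second model.** This one uses constant per-visit hazards of recovery (from visit 2, because recovery needs two consecutive visits) and of exit. There are 16 weekly visits (SAM) or 8 fortnightly visits (MAM), and the hazards are solved to give the stated Table 2 proportions.

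- *Level.* With true recovery at 75%, one minus Kaplan-Meier is 78% at 5% exits, 82% at 10%, 86–87% at 15% and 91–92% at 20%.
- *Difference.* A true 6-point deficit appears as 1.8–2.6 points if it runs through exits and as 6.4–7.5 points if it is slower recovery with equal exits (control exits 5–15%). If half runs through exits (control exits 10%), it appears as 4.6–4.7 points.

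**5. Effect on the verdict.** Simulation with 798 per arm, a true 6-point deficit, a 6-point margin, a 95% interval (Greenwood standard error for Kaplan-Meier) and 40,000 runs per case:

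| Analysis and route of the deficit | Control exits | Non-inferiority declared |
|---|---|---|
| Table 2 proportion, any route | 5–15% | about 2.5% |
| KM, all through exits | 5–15% | 34–55% |
| KM, half through exits | 10% | 8–10% |
| KM, slower recovery only | 10% | about 1% |

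With 725 per arm the all-exits row is 32–51%.

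**The case against.** The strongest reply is that the protocol never says these children are censored. Each has a final outcome of not recovered, analysis is by intention to treat, and the Chi-square rule fits a recovered/not recovered endpoint. The sample size uses proportions, and the monitoring board reviews children already classified one way or the other. The Kaplan-Meier sentence could be only a supplementary display of time to recovery. The article is also condensed, and censoring rules usually belong in the analysis plan.

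Much of this stands. The censoring is inferred from usual practice, the proportion may well be the intended test, and the absence of a censoring rule is not itself the point. What remains is that the article does state a method for recovery rates, in the same words as its powered objective. As ordinarily applied, that method does not estimate the Table 2 endpoint. The Chi-square sentence does not resolve this, because nothing says which of the two decides non-inferiority.

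A reader might also infer that the bias always hides a deficit and so favours a reduced dose. The documents do not support that. The direction depends on the route: slower recovery with equal exits widens the apparent deficit, and slower recovery is a plausible route for a smaller ration. Nor does the description fit the MAM trial, where one experimental arm is an increased dose and the other swaps RUSF for RUTF. Deterioration to SAM is an exit only in that trial.

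**Conclusion.** The point holds in conditional form. If recovery rates are estimated by ordinary Kaplan-Meier, recovery is overstated against the protocol's own endpoint: by 9.7 points (84.7% against 75%) with 15% exits spread evenly, and by about 3 to 17 points for exits of 5% to 20% in the second model. A true 6-point deficit could appear as about 2.7 or about 7.4 points according to its route, which is enough to change a verdict at the 6% margin.

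These sizes rest on assumed exit rates and timings, since the documents give none, and on the usual censoring convention, which the article does not state. If exits are kept as unrecovered to week 16 and nothing else is censored, there is no discrepancy. The same method sentence covers relapse, but no calculation was made for relapse and no size is claimed there. The 798 per arm is unaffected.

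**What to change.** In Statistical analyses, state that the non-inferiority test in trials 1 and 2 is based on the difference between each experimental arm and control in the proportion recovered by 16 weeks. Use the Table 2 classification, all randomised children in the denominator, and the confidence interval of that difference compared with the margin.

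Show time to recovery by the cumulative incidence function (Aalen-Johansen), with death, hospitalization, loss to follow-up and, in the MAM trial, deterioration to SAM as competing events. Do not report one minus Kaplan-Meier as the recovery rate.

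The cost is a change of wording in the protocol or analysis plan. The method is in standard software, and no further children or data are needed.
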